### Randomisation

Participants will be randomly assigned to either an intervention or control group of equal size (20 in each arm), using the web-based randomisation service (http://www.sealedenvelope.com). Group assignment will be recorded in a database, and the result of each randomisation emailed to the trial administrator.

Before consenting to participation in the study, respondents will be informed that there is a 50/50% probability of being assigned either to the intervention or control arms. This is to ensure that participants understand the study design and the fact that, although everyone will eventually be able to access the intervention, those in the control arm will not be able to do so straight away. Instead, control arm participants will be informed that they will be given access after completing a three-month follow-up.

### Statistical analysis plan

Demographic data will be analysed using basic descriptive statistics. Recruitment and retention rates into both arms will be calculated. We shall examine univariate associations of the outcome measures, using parametric or non-parametric tests as appropriate. We shall conduct exploratory tests of change during the course of the intervention using paired measures, such as the Wilcoxon paired-samples test or a *t* test, as appropriate according to the data.

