**Discussion:**

The proposed trial will demonstrate the feasibility of conducting a fully powered RCT to evaluate the efficacy of an e-learning resource about schizophrenia with African-Caribbean families. Qualitative work will explore the intervention’s accessibility and barriers/facilitators to participation, including attitudes to randomisation. These data will facilitate further refinement of the intervention.

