## Aims of the trial

The aim of the study is to test the feasibility of implementing and evaluating a non-commercial e-learning resource among African-Caribbean families with schizophrenia family members in order to improve their knowledge and attitudes about the illness and about psychosis in general. The feasibility of recruitment, data collection, retention, and views on the intervention’s acceptability will inform a larger-scale RCT. This feasibility pilot has three primary outcomes:i.Recruitment of relatives and carers of people with schizophreniaii.Participant retentioniii.Participant attrition

Secondary outcomes include:iv.Improved knowledge about schizophrenia and psychosisv.Improved attitudes about schizophrenia and psychosisvi.Acceptability of the intervention

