### Participants and recruitment

We shall recruit 40 relatives and carers of African-Caribbean persons diagnosed with schizophrenia or other non-affective psychosis (DSM-V schizophrenia or ICD-10 F20-29: schizophreniform disorder, schizoaffective disorder, delusional disorder, or psychosis not otherwise specified). The sample size is based on previous community psychoeducation studies that report equivalent or smaller sample sizes as appropriate for assessing the feasibility of novel psychoeducation interventions [11, 34–36]. Recruitment will be facilitated by support from relevant organisations, such as the National Institute for Health Research (NIHR’s) Clinical Research Network (CRN), African and Caribbean Mental Health Services (a non-governmental organisation (NGO)), community centres, and patient and carer advocacy and support services. We shall raise awareness of the study in African-Caribbean communities via community engagement events, newspapers and radio, and social media.

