## Discussion

This pilot trial is unique in evaluating the feasibility and acceptability of a novel, culturally-appropriate e-learning intervention to improve knowledge and attitudes about schizophrenia and psychosis in African-Caribbean families. According to the authors’ knowledge, it is also the only psychoeducation intervention for schizophrenia spectrum disorders that has been co-produced with African-Caribbean stakeholders. This pilot trial will examine the feasibility of recruiting and retaining participants from an ethnic group most likely to be diagnosed with schizophrenia spectrum disorders and among the least likely to receive psychoeducation. To inform further development of the intervention and a larger, fully-powered trial of its cost and clinical-effectiveness, we shall also assess the feasibility of collecting relevant outcome data. Importantly, for a community that regards itself as being ‘seldom heard’ versus ‘hard-to-reach’ [50] as commonly reported, we shall also evaluate African-Caribbean families’ perspectives on the intervention acceptability, accessibility, and utility.

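### The only analyses named for the Ca-KAP, ASMI and SF-12 scores are significance tests, which suit a 20-per-arm pilot for a larger RCT less well than estimates with intervals

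*Protocol article*

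**What the plan says.** The Statistical analysis plan section of the protocol article assigns an analysis to each kind of data.

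- Demographics: "Demographic data will be analysed using basic descriptive statistics".
- Primary feasibility outcomes: recruitment and retention rates are to be calculated for each arm.
- Outcome measures: "We shall examine univariate associations of the outcome measures, using parametric or non-parametric tests as appropriate". In addition there are exploratory paired tests of change over the course of the intervention, by Wilcoxon or t test.

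On SF-12, the Outcomes and measures section says that scores at the three time points will be examined for preliminary data on whether carers' health has improved. It names no summary statistic.

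On size, Participants and recruitment gives 40 people, and Randomisation splits them 20 to each arm. The stated basis is precedent: "The sample size is based on previous community psychoeducation studies that report equivalent or smaller sample sizes as appropriate for assessing the feasibility".

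On purpose, the Abstract says "The proposed trial will demonstrate the feasibility of conducting a fully powered RCT to evaluate the efficacy of an e-learning resource". Aims of the trial says that the feasibility of recruitment, data collection and retention, with views on acceptability, "will inform a larger-scale RCT". The Discussion looks ahead to "a larger, fully-powered trial of its cost and clinical-effectiveness".

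**The concern.** A fully powered trial with a score as its outcome needs the SD of that score. Because baseline is measured here, it can also use the correlation between baseline and follow-up. A p-value supplies neither. Nothing in the protocol sizes the pilot for testing, so a non-significant result would say little about whether the resource works. A significant result would be hard to tell from chance or from an overestimated effect. If the results section follows the stated plan and reports tests only, the team planning the next trial would have to go back to the raw data for the figures it needs, and readers might take the p-values as early evidence on efficacy.

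**Working it through.** **Inputs from the protocol.** 40 participants, 20 per arm (20 + 20 = 40, consistent); three time points; paired tests of change. No alpha, power, effect size, SD or dropout rate is given, so the sample size has no calculation to reproduce.

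**Assumptions.** Two-sided alpha 5%; target power 80%; 80% retention as an illustration (0.8 × 20 = 16 per arm); t-based power.

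**1. Paired test within one arm.** The noncentrality is dz × √n on n − 1 df, where dz is the mean change divided by the SD of the change. Power of 80% needs a noncentrality of 2.954 at 19 df and 2.998 at 15 df.
- n = 20: dz = 2.954 / √20 = 0.66.
- n = 16: dz = 2.998 / √16 = 0.75.

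In units of the score's own SD, multiply by √(2(1 − r)), where r is the correlation between the two occasions. With 20 pairs this gives 0.66 × 1.18 = 0.78 SD at r = 0.3, 0.66 SD at r = 0.5, and 0.66 × 0.775 = 0.51 SD at r = 0.7.

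**2. Between-arm test.** The noncentrality is d × √(n/2) on 2n − 2 df. With n = 20, power of 80% needs 2.875, so d = 2.875 / √10 = 0.91. Power at smaller effects:

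| n per arm | d = 0.3 | d = 0.5 | d = 0.8 |
|---|---|---|---|
| 20 | 15% | 34% | 69% |
| 16 | 13% | 28% | 59% |

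**3. What estimation would give.** A pooled SD from 40 people has 38 df. The 95% interval for the variance is the estimate times 38/56.90 = 0.67 to 38/22.88 = 1.66. For the SD this is 0.82 to 1.29 times the estimate. Required sample size is proportional to the variance, so 0.67 to 1.66 is also the range for the next trial's N at a fixed raw difference. With 32 people (30 df) the range is 0.64 to 1.79. An observed correlation of 0.5 at n = 40 has a Fisher interval of tanh(0.549 ± 1.96/√37) = 0.22 to 0.70.

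**4. Why the correlation is worth reporting.** With baseline adjustment, n per arm = 2 × ((1.96 + 0.84)/d)² × (1 − r²). At an assumed d = 0.4 and 80% power this is 99 per arm at r = 0, 74 at r = 0.5 and 51 at r = 0.7. The correlation alone can move the next trial's size by about half.

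**The case against.** The strongest reply is that this is a short paragraph in a journal article, and that means, SDs and intervals are commonly left to a full analysis plan. That has weight. The sentence on demographics does not say that descriptive statistics are for demographics only. A reader might infer that the plan excludes summaries of the scores, but the text does not say so. What remains is that the article does choose an analysis for the scores, and the choice is testing. That is a stated method and open to comment.

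A reader might also infer that the plan contradicts its own aim. It does not. Aims of the trial lists recruitment, data collection, retention and acceptability as what will inform the larger trial, and no passage promises a variance for sizing it. The primary outcomes are to be estimated as rates. The scores are secondary, and the tests of change are already called exploratory, although the association tests are not.

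Nor is the information lost. A paired t test needs the SD of the change, the association analyses might include correlation coefficients, and every quantity can be computed from the data.

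Finally, one might conclude that a false positive is nearly certain, given several measures with subscales. The protocol does not say how many tests will be run, and scores from the same people are correlated, so no such figure can be attached to it.

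**Conclusion.** The point holds as a mismatch between the analysis named for the secondary scores and the purpose of the pilot. It is something to consider and does not affect the primary feasibility outcomes. With 20 per arm the tests have 80% power only for a paired standardised change of about 0.66 (0.75 with 16 pairs) or a between-arm difference of about 0.91 SD. These figures assume two-sided 5% tests, and 80% retention for the 16 pairs. The paired figure becomes less demanding in score units if the two occasions are highly correlated. The imprecision of an SD from 40 people comes from the sample size and would exist under any analysis. It is a reason to report intervals, not a fault in the choice of tests.

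**What to change.** In the Statistical analysis plan section, make estimation the analysis of Ca-KAP, ASMI and SF-12:

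- by arm and time point, the number complete, mean and SD;
- the change and the between-arm difference as estimates with 95% CIs;
- the pooled SD and the baseline-to-follow-up correlation, each with a confidence interval, for planning the larger RCT.

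Label any tests that are kept as exploratory and secondary to the estimates, and state that no efficacy conclusion will be drawn from them. A ban on p-values is not needed, and how the uncertainty in the SD is carried into the next sample size can be left to that trial's team.

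The cost is a few sentences of wording and no new data. The downside is that the pilot makes no significance-based statement about efficacy.

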## Method

### Study design

The study is a parallel, two-arm feasibility RCT examining relatives’ and carers’ knowledge and attitudes about schizophrenia at three time-points: pre-intervention, post-intervention, and 3-month follow-up.

The intervention will not be tested against a comparator. Instead, participants in the control arm will be administered the standardised measures without accessing a learning resource about schizophrenia. They will be provided access to the learning resource upon the completion of data collection (Fig. 1).

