#### Attitudes to severe mental illness scale

Attitudes to Severe Mental Illness Scale (ASMI) is a validated assessment [47] which draws from a number of older standardised measures of attitudes to mental illness, such as the Opinion on Mental Illness (OMI) Scale and Community Attitudes to Mental Illness (CAMI). ASMI was selected by stakeholders in phase 2 focus groups as the most acceptable attitudes measure out of five assessments. The stakeholders liked the relatively short length of this 30-item questionnaire. They also found the wordings of the items accessible. ASMI consist of four subscales (stereotyping, optimism, coping, and understanding) comprising 30 statements about people with mental illness, such as “People with severe mental illness are failures”, “A person with severe mental illness can be trained in an occupation”, and “The friends should not abandon a person when he/she is suffering from severe mental illness”*.* Respondents are asked to rate their degree of agreement/disagreement with each statement on a Likert scale with scoring as follows: “agree” (4), “rather agree” (3), “rather disagree” (2), “disagree” (1), to “do not know” (0). Negatively worded items are reverse scored. A high total score reflects a positive attitude towards persons with mental illness.

#### SF-12 version 2

Adopted from SF-36 [48], SF-12 v2 is a practical, reliable, and valid self-reported measure of functional health 12 questions to and well-being. It is widely used to monitor population health, analyse disease burden, and predict costs and is particularly useful at the community level as it can be completed in 2–3 min. A preference-based utility index (SF-6D) has been developed from the SF-12 to facilitate economic evaluation and estimate quality-adjusted life years (QALYs). This will be important for future studies. However, in this study, we shall examine scores before and after and at the 3-month follow-up to provide preliminary data on whether using the learning resource has improved relatives’/carers’ health.

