### Quantitative data collection

Participants accessing the intervention online will be provided a choice between completing electronic versions or hard copies of the measures. Participants using the DVD version will complete hard copies of the measures. The control group will complete the same measures at the same time points. However, they will access the intervention only after the collection of time point 3 outcome data. Participants will be informed of this procedure prior to collecting consent.

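### The only named test of change is a paired before/after test; the secondary scores need an explicit baseline-adjusted comparison between the randomised arms

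*Protocol article*

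**What the plan says.** The Study design section describes a "parallel, two-arm feasibility RCT examining relatives’ and carers’ knowledge and attitudes about schizophrenia at three time-points". The Randomisation section allocates 20 participants to each arm. Under Quantitative data collection, "The control group will complete the same measures at the same time points", and controls get the resource only after the last assessment.

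The Statistical analysis plan section says three things that bear on this point:
- "Recruitment and retention rates into both arms will be calculated". This is the only quantity in that section that is reported by arm.
- "We shall examine univariate associations of the outcome measures, using parametric or non-parametric tests as appropriate". Randomised arm is not mentioned.
- The authors will conduct "exploratory tests of change during the course of the intervention using paired measures, such as the Wilcoxon paired-samples test" or a t test, depending on the data.

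Two other places affect how the results would be read. The SF-12 version 2 paragraph says "we shall examine scores before and after and at the 3-month follow-up to provide preliminary data on whether using the learning resource has improved" the health of relatives and carers. The Study design section says "The intervention will not be tested against a comparator", and then explains that controls complete the measures without the resource and receive it later.

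**The concern.** A paired test asks whether scores moved over time in the people tested. It does not ask whether the resource moved them. The same knowledge questionnaire is given three times to people who have volunteered for a study about schizophrenia. Scores can rise through familiarity with the items, through reading elsewhere, or through regression to the mean. A concurrent randomised control arm removes these influences, and this trial has one. If the named method is the one reported, the secondary question on knowledge, attitudes and quality of life can receive a confounded answer. The most prominent outcome result passed to the larger trial would then be a within-arm p-value. Planning that trial calls for a between-arm difference, a residual SD and a baseline correlation.

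**Working it through.** **No figure to reproduce.** The sample size of 40 rests on precedent from earlier studies. The article gives no alpha, power, effect size, SD or dropout rate. The allocation is consistent: 20 + 20 = 40.

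**Inputs.** From the article: 20 per arm, three assessments, the same measures in both arms. Assumed, because the article gives no values: two-sided alpha 0.05, normal scores, full retention, no effect of the resource, a gain *g* common to both arms (in baseline SDs), and a pre-post correlation *r* of 0.5 or 0.7.

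**Paired t test in the intervention arm.** The SD of the change is √(2(1−r)), so the noncentrality is g·√20 / √(2(1−r)), referred to noncentral t on 19 df.
- g = 0.2, r = 0.5: SD of change √1.0 = 1.00; noncentrality 0.2 × 4.472 = 0.89; significant in 13.6%.
- g = 0.5, r = 0.7: SD of change √0.6 = 0.775; noncentrality 0.5 × 4.472 / 0.775 = 2.89; significant in 78.2%.

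**ANCOVA between arms** (follow-up score on arm plus baseline) and the **Wilcoxon** test were simulated under the same conditions, with 20,000 trials (3,000 for Wilcoxon).

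| Common gain, no effect of resource | Paired t, r = 0.5 | Paired t, r = 0.7 | Wilcoxon, r = 0.5 / 0.7 | ANCOVA, r = 0.5 / 0.7 |
|---|---|---|---|---|
| 0 | 5% | 5% | 4% / 5% | 5.0% / 4.8% |
| 0.2 SD | 14% | 20% | 13% / 19% | 5.0% / 5.1% |
| 0.3 SD | 25% | 38% | 23% / 35% | 4.9% / 4.7% |
| 0.5 SD | 57% | 78% | 55% / 76% | 4.7% / 5.1% |

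With 16 per arm (an assumed 20% loss), the paired t test is still significant in 20% to 31% at 0.3 SD and 47% to 68% at 0.5 SD.

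**Precision of the alternative.** The 95% CI half-width for the between-arm difference, with 20 per arm, is:
- post scores only: √(2/20) × t(38) = 0.316 × 2.024 = 0.64 SD;
- ANCOVA: √((2/20)(1−r²)) × t(37). At r = 0.6 this is √0.064 × 2.026 = 0.51 SD.

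The difference detectable with 80% power, (1.96 + 0.84) × √(2(1−r²)/20), is 0.89 SD unadjusted, 0.77 SD at r = 0.5 and 0.63 SD at r = 0.7. The useful output is therefore an estimate with its interval, not a significance test.

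**The case against.** The strongest defence is that nothing decisive depends on these tests. The primary outcomes are recruitment, retention and attrition, and these are to be compared by arm. Knowledge and attitudes are secondary, the tests are called exploratory, the SF-12 reading is called preliminary, and efficacy is left to a fully powered trial. This stands, and it limits the priority. It does not change what a paired test estimates.

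The plan is also a short summary in an article, and a fuller one may exist. The covariates and the analysis set could properly be left to it, so a missing ANCOVA model is not in itself the fault. The point concerns the method that the article does state and the reading that it gives to SF-12 scores.

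The percentages in the table are the power to detect a real change over time. They become false-positive rates only if that change is attributed to the resource. This is correct, and the gain and correlation are assumed. Practice effects are also more plausible for a knowledge questionnaire than for ASMI or SF-12.

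Four stronger readings are tempting, and the article does not support them:
- *Gains will be read as an effect of the resource on every measure.* Only the SF-12 paragraph makes that link. The analysis section speaks only of change.
- *The plan rules out comparing the arms.* Read with the sentence after it, the Study design statement about a comparator means that there is no active comparator. The univariate associations might include arm, although the text does not say so.
- *The arms will be contrasted by which one reaches significance.* The article does not say this, nor whether the paired tests are run per arm or pooled. Neither would estimate the effect of the resource.
- *The quantities needed for the main trial are lost.* They can be computed from the data that will be collected.

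**Conclusion.** The point holds at moderate priority. The one named test of change for the secondary scores is a paired before/after test, no between-arm comparison of those scores is explicit, and the SF-12 paragraph treats before/after scores as evidence of benefit. With no effect of the resource, an assumed common gain of 0.2 to 0.5 SD and an assumed correlation of 0.5 to 0.7, a paired t test in an arm of 20 is significant in about 14% to 78% of trials. ANCOVA between arms stays at about 5%. At zero gain both are at about 5%, so the size depends wholly on the assumed gain. The direction does not: any common gain above zero takes the paired test above its nominal level as a test of the resource. The feasibility conclusions are not affected.

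**What to change.** In the Statistical analysis plan section, state that at post-intervention and at 3 months the between-arm difference in Ca-KAP, ASMI and SF-12 will be estimated by ANCOVA. The model is the follow-up score on arm plus the baseline value of the same score, with participants analysed in the arm to which they were randomised. Report the adjusted difference with its 95% CI, together with the residual SD and the baseline correlation for planning the main trial. Present within-arm change as description only, without tests.

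Reword the SF-12 paragraph so that any statement about improvement refers to the between-arm difference. In Study design, clarify that there is no active comparator and that the control condition is delayed access to the resource.

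The cost is a few sentences and no new data. The downside is a wide interval with 20 per arm (about ±0.51 SD if the correlation is 0.6), which is an accurate statement of what a pilot of this size can show.

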### Qualitative data collection

Qualitative data on acceptability of the intervention will be collected via semi-structured interviews using a specially developed interview schedule (available on request). The schedule comprises 13 questions about participants’ experiences of using the intervention, covering usability, appearance, content, interactive features, and the extent the intervention meets the needs of African-Caribbean families affected by schizophrenia.

